### Outcome measures

The preintervention (T0) assessment will include sociodemographic questions (age, gender, relationship status, education and language most spoken at home), and any previous knowledge and experience of breast, cervical or colorectal cancer among family and friends.

To evaluate the efficacy of the AWACAN-ED public toolkit, we will measure two outcomes before (T0) and at two points after the intervention (T1: 15 min after the intervention; T2: 1 month after the intervention): recall of symptoms (primary outcome) and intention to seek help (secondary outcome). See study instrument in online supplemental material 1.

To assess recall of symptoms, an open-ended question will be used: *“Please would you name as many symptoms or signs of [breast, cervical, or colorectal] cancer as you can think of?”*.^27^ Responses will be recorded verbatim and will be coded by two researchers in each country against an agreed list of symptoms from the AWACAN survey for breast (15 symptoms) and cervical (11 symptoms) cancer awareness^27^ and from the Bowel Cancer Awareness Measure (9 symptoms).^28^ Participants will score ‘1’ if they mention a symptom that corresponds to the list of symptoms, and ‘0’ if they do not mention it and summed to produce total score of the number of recalled symptoms for each cancer type.

Intention to seek help will be measured by asking participants to report how soon they would visit the pharmacy or clinic or health centre or hospital, if they noticed symptoms of possible breast, cervical and colorectal cancer^27^ with five response options (‘never’, ‘less than 1 week’, ‘between a week and 1 month’, ‘between a month and 3 months’ and ‘3 months or more’). Only women will be asked the items about seeking help for breast or cervical symptoms. For analysis, responses will be dichotomised to ‘less than 1 week’ and ‘more than 1 week’.

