### Sample size and data analysis plan

Participant characteristics and outcomes will be summarised using descriptive statistics, including mean and median, SD and IQR. To assess how engaging participants found the health communication tools, we will use descriptive statistics to report the proportion of participants who agreed with each aspect of engagement. For the open response question, two researchers will independently code the responses into thematic categories.

We have estimated the sample size based on the assumption that the baseline number of expected recalled symptoms before the intervention will be equivalent to the average number of breast cancer symptoms recalled in South Africa using the same measure.^32^ The expected effect of the intervention on symptom recall was assumed to match or exceed the increase observed in a comparable study of lung cancer symptom recall in the UK^33^ that had a more conservative impact than a recent quasi-experimental study in South Africa.^34^ Based on these assumptions, a sample size calculation for a paired t-test with a significance level (α) of 0.05 and a power of 80% resulted in an estimated requirement of 144 participants per intervention group (N=432). This will be distributed across the two settings in South Africa and two in Zimbabwe (see table 1). To allow subgroup analyses by gender, age band and language, we will recruit at least 20 participants to each category and recruit twice as many women (n=288) as men (n=144). We anticipate minimal missing data as the questionnaires will be administered by experienced fieldworkers and researchers. However, listwise deletion will be used if any data is missing at random. Statistical analyses will be conducted using R software (2021).^35^

**Table 1 T1:** Planned minimum sample sizes required and distribution by intervention group

Research site	Intervention groups			Total
	Breast cancer tool	Cervical cancer tool	Colorectal cancer tool	
South Africa (Western Cape)				
Urban	36	36	36	108
Rural	36	36	36	108
Zimbabwe (Harare)				
Urban	36	36	36	108
Rural	36	36	36	108
Total	144	144	144	432

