### Data collection and management

Prior to the start of the study, the questionnaire items will be piloted in English with at least two participants in each community site in both countries (n=8). We will then translate and pilot the questionnaire items into Afrikaans, isiXhosa, Ndebele and Shona using the following steps^36^:

Forward and backward translations^37^ undertaken by professional translators and bilingual fieldworkers per each language.‘Expert’ review: AWACAN-ED team members and/or other cancer researchers fluent in both English and the local language will evaluate the translations and reconcile discrepancies.Interviews will be conducted with local language speaking community participants using the Afrikaans and isiXhosa version (SA, n=4), and the Ndebele and Shona version (ZIM, n=4) to clarify meaning and understanding of each item.

Data will be collected by experienced fieldworkers using a hand-held electronic tablet customised with the questionnaire and loaded with the RedCap software. Participants will be assigned a participant ID code so that their data is not linked to their identity. For sociodemographic characteristics, participants will have the option to not answer questions related to their relationship status and education level. These cases will be treated as missing data.

The study team will meet weekly and the independent study steering committee will meet quarterly to monitor data. Any protocol modifications will be reported to the trial registry. On completion of the study, team anonymous digital data will be available from the University of Cape Town following an embargo period of 12 months after project completion.

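### Listwise deletion is tied to data missing at random, a condition under which it is not generally valid; 1-month recall is the outcome most exposed

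*Protocol article*

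**What the plan says.** Under *Sample size and data analysis plan* the article expects few gaps: "We anticipate minimal missing data as the questionnaires will be administered by experienced fieldworkers and researchers". It then fixes the rule: "listwise deletion will be used if any data is missing at random". It names no other method for missing data.

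Under *Outcome measures*, recall (the primary outcome) is taken before the intervention (T0) and twice after it: "T1: 15 min after the intervention; T2: 1 month after the intervention".

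Under *Data collection and management*, "participants will have the option to not answer questions related to their relationship status and education level. These cases will be treated as missing data".

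Only one test is named, the paired t-test behind the sample size of 144 per group. The planned subgroups are gender, age band and language. No outcome analysis is said to use education or relationship status.

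**The concern.** The condition and the method do not match. Data are missing at random when the chance of being missing depends only on observed quantities, such as recall at an earlier visit. People who were observed then differ systematically from those who were not. Deleting the incomplete cases leaves a selected sample, unless the analysis conditions on whatever drove the selection. A paired t-test conditions on nothing.

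This is a rule the article states, so it is not a detail left to a separate analysis plan.

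The reason given for expecting few gaps, skilled interviewers, addresses skipped items. It says little about people not being reached a month later. If those who recalled less are harder to reach, the T2 estimate of the primary outcome can be biased. The wording also reaches any missing item, so a literal reader could apply it across the whole dataset.

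**Working it through.** **The plan's own figure.** The article gives neither an effect size nor an SD, so 144 cannot be reproduced forwards. Solving a two-sided paired t-test for 80% power at n = 144 gives a standardised change d = 0.235 (normal approximation (1.960 + 0.842)/√144 = 0.233). It is used below only to set a plausible scale.

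**Assumptions, none from the documents.** Recall is treated as normal with SD 1 at each visit. The probability of being seen at T2 is 1/(1 + exp(−(1.55 + b·Y))), where Y is earlier recall. The slope b and the correlations ρ are varied.

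**Check 1: paired T0–T2 change, loss depending on T0 recall.** Let m be mean T0 recall among those retained, in SD above the full-sample mean. The listwise estimate is

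δ + (ρ − 1)·m, with true change δ = 0.235·√(2 − 2ρ).

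Numerical integration gives m = 0.090 for b = 0.5 (loss 18.6%) and m = 0.185 for b = 1.0 (loss 21.4%).

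| ρ | True δ | b = 0.5, formula | b = 1.0, formula | Simulated (b = 0.5; 1.0) |
|---|---|---|---|---|
| 0.3 | 0.278 | 0.278 − 0.7 × 0.090 = 0.215 | 0.278 − 0.7 × 0.185 = 0.149 | 0.218 (−22%); 0.155 (−44%) |
| 0.5 | 0.235 | 0.235 − 0.5 × 0.090 = 0.190 | 0.235 − 0.5 × 0.185 = 0.143 | 0.192 (−18%); 0.142 (−40%) |
| 0.7 | 0.182 | 0.182 − 0.3 × 0.090 = 0.155 | 0.182 − 0.3 × 0.185 = 0.127 | 0.155 (−15%); 0.128 (−30%) |

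Each simulated cell is 3,000 samples of 144. The formula puts the worst cell at −46% rather than −44%; the gap is simulation error. Coverage of the 95% interval ran from 0.93 down to 0.81. With b = 0 (completely at random) the bias was about 1% or less. An estimate conditioning on T0, using everyone's T0 score, was within about 2% throughout.

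**Check 2: between-arm T2 effect, loss depending on T1 recall.** Assume a tool effect of 0.5 SD at T1 and 0.30 SD at T2, with 144 exposed and 288 unexposed to a given tool. The complete-case difference is

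0.30 + ρ₁₂·(m_E − m_C),

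where m_E and m_C are the mean T1 excess over the arm's own mean among those retained.

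- b = 0.7 (loss 15.0% exposed, 19.6% unexposed): m_E − m_C = 0.098 − 0.128, or −0.029 before rounding. ρ₁₂ = 0.4 gives 0.30 − 0.012 = 0.288; ρ₁₂ = 0.6 gives 0.30 − 0.017 = 0.283.
- b = 1.0 (loss 15.0% and 21.4%): 0.132 − 0.185, or −0.052 before rounding. ρ₁₂ = 0.4 gives 0.279; ρ₁₂ = 0.6 gives 0.269.

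Moving the intercept so that overall loss runs from about 14% to 21% keeps the result at 0.27–0.29. A likelihood estimate that uses T1 returned 0.300–0.301 in simulation.

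**Check 3: mechanisms that do little harm.** With T0-dependent loss equal in all arms, the simulated between-arm difference was 0.299 against 0.300. With loss depending on T0 in one arm only, the unadjusted change-score difference was 0.208 or 0.394, but complete-case ANCOVA on T0 gave 0.301.

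**Check 4: the literal reading.** If everyone without T2 is also removed from the T1 analysis, the exposed T0–T1 change becomes 0.50 + (1 − ρ₀₁)·m_E. With ρ₀₁ = 0.4–0.6 and the values of Check 2, that runs from 0.50 + 0.4 × 0.098 = 0.54 to 0.50 + 0.6 × 0.132 = 0.58. Unexposed participants, with no true change, show 0.4 × 0.128 = 0.05 to 0.6 × 0.185 = 0.11.

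**The case against.** The strongest reply is that the effect may be small. The between-arm bias in Check 2 is 0.012–0.031 SD. With roughly 122 and 227 people left, the standard error is about √(1/122 + 1/227) = 0.11 SD, so the bias is about a tenth to a little over a quarter of one standard error, towards the null. Complete-case analysis remains valid if the model conditions on what drives the loss. Retention may also be good, since *Ethics* sets the participant payment after data collection is complete. All of this stands. It limits the size of the problem but does not make the stated rule correct, and the article does not commit to a model that conditions on earlier recall.

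Three stronger readings are tempting and are not supported.

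- *The rule will discard everyone who declines education or relationship status.* The article says only of such answers that "These cases will be treated as missing data". Listwise deletion ordinarily removes a case only from analyses using the missing variable, and no outcome analysis is said to use these two. Such people could be dropped if the variables enter a model or deletion runs across the whole dataset.
- *The T1 result is contaminated.* A T0–T1 comparison does not use T2. The inflation in Check 4 needs whole-dataset deletion, which the wording allows but does not require.
- *The rule costs the trial its 80% power.* At d = 0.235, power is 75.8% with 130 people and 70.5% with 115. That loss comes mainly from absent follow-up; a better model recovers only part of it. The article calls 144 a planned minimum and does not say that T2 is the powered visit.

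**Conclusion.** The point holds, at moderate severity. The article attaches listwise deletion to a condition that does not generally justify it, and this bears on 1-month recall, part of the primary outcome. Under the assumed mechanisms, a between-arm T2 effect of 0.30 SD is estimated at about 0.27–0.29 SD, and the paired T0–T2 change is 15–44% low in simulation. These figures rest on assumed loss of 14–21% and 19–21% respectively, on assumed correlations and slopes, and on treating a symptom count as normal. The documents fix none of these. Both size and direction depend on the mechanism, and some mechanisms give essentially no between-arm bias. It cannot be concluded that the trial's result will be biased. What can be concluded is that the rule does not protect against bias in the situation it names. Removal from T1 analyses, or for declined demographic items, is an ambiguity in the wording.

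**What to change.** Replace the sentence on listwise deletion, before analysts see outcome data, with wording to this effect:

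1. Recall is analysed with a method valid under missing at random: for example, a likelihood-based repeated-measures model using every available T0, T1 and T2 score, or multiple imputation that includes earlier recall.
2. T1 is analysed on everyone with a T1 score, whether or not T2 was obtained.
3. A declined answer on education or relationship status does not remove a participant from any outcome analysis. If either variable is used, declining forms its own category or is imputed.

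Complete-case analysis can stay as a secondary analysis, with its condition stated correctly. The cost is a change of wording and slightly more work in R, which the plan already uses; data collection does not change.

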### Data collection and management

Prior to the start of the study, the questionnaire items will be piloted in English with at least two participants in each community site in both countries (n=8). We will then translate and pilot the questionnaire items into Afrikaans, isiXhosa, Ndebele and Shona using the following steps^36^:

Forward and backward translations^37^ undertaken by professional translators and bilingual fieldworkers per each language.‘Expert’ review: AWACAN-ED team members and/or other cancer researchers fluent in both English and the local language will evaluate the translations and reconcile discrepancies.Interviews will be conducted with local language speaking community participants using the Afrikaans and isiXhosa version (SA, n=4), and the Ndebele and Shona version (ZIM, n=4) to clarify meaning and understanding of each item.

Data will be collected by experienced fieldworkers using a hand-held electronic tablet customised with the questionnaire and loaded with the RedCap software. Participants will be assigned a participant ID code so that their data is not linked to their identity. For sociodemographic characteristics, participants will have the option to not answer questions related to their relationship status and education level. These cases will be treated as missing data.

The study team will meet weekly and the independent study steering committee will meet quarterly to monitor data. Any protocol modifications will be reported to the trial registry. On completion of the study, team anonymous digital data will be available from the University of Cape Town following an embargo period of 12 months after project completion.

## Discussion

To our knowledge, this is the first RCT across South Africa and Zimbabwe to evaluate the efficacy and acceptability of a cancer awareness communication intervention using locally tailored health infographics which combine pictures and text to depict symptoms of breast, cervical and colorectal cancer. The study will provide findings around the potential effect of these locally tailored health infographics in improving symptom awareness. This could produce insights for policy makers to incorporate into cancer prevention and early detection programmes and healthcare providers who could use these health infographics to better engage with patients by providing culturally appropriate information.

The major strength of the study is the community codesign of the intervention ensuring a culturally sensitive toolkit in five languages for local use across two Southern African countries, which may contribute to the acceptability of the tools as well as facilitate participant recruitment. The toolkit has been carefully designed to minimise anxiety and the current study will test this to provide evidence that campaigns using these resources are unlikely to cause distress. Although the study will evaluate the efficacy of the health infographics on cancer symptom awareness in some of the most commonly spoken languages in the research settings, future adaptations will be required to develop and evaluate the AWACAN-ED public toolkit for use in other regions with different local languages and cultural requirements to ensure contextual suitability, and in wider settings to ensure generalisability. Similarly, the toolkit could be developed for symptoms of other common cancers such as prostate, lung and oesophagus. The longer-term impact (beyond 1 month) and measurement of the effect on actual help-seeking behaviour is not possible in the time frame of this study. There are elements of this study that could be investigated further in future research, including whether participants seek information about other cancers after being exposed to information about one cancer. Further research studies will also be required to evaluate the impact of the toolkit on healthcare use and investigate the necessary efforts and health systems adaptations (eg, improving human resources and coordination between primary care and specialist levels) needed to respond to the future burden of breast, cervical and colorectal cancer in Southern Africa.

## Ethics and dissemination

### Ethics

Ethical approval was first obtained on 14 April 2025, reference number 148/2025 in South Africa (UCT) and then by the Ethics Committee of the University of Harare (Zimbabwe). This study has been categorised as low risk. There are no expected adverse events related to the intervention or research procedures. All participants will be required to provide written informed consent prior to participation, and they will receive R200/US$10 after data collection completion as compensation for the time given to the study. The trial was registered in the Pan African Clinical Trials Registry (ref num. PACTR202505475803308) on 28 May 2025.

### Dissemination

The study findings will be disseminated through peer-reviewed publications, conference presentations, community workshops and reports published on the AWACAN-ED programme website. Findings of the study, including feedback and suggestions from the community workshops regarding dissemination plans, will also inform future national public awareness campaigns, as well as potential tailored community-based behavioural interventions to reduce appraisal and help-seeking intervals for patients with symptoms of possible breast, cervical and colorectal cancer in South Africa and Zimbabwe. All future dissemination activities will be implemented in collaboration with communities, relevant cancer prevention organisations (eg, CANSA) and other clinical and non-clinical stakeholders (eg, primary healthcare workers, policy makers).

## Trial status

The recruitment of participants started on 21 July 2025 with completion due by June 2026.
